### Intervention: Learn to *b*e *s*afe with Emmy and friends™

*Learn to be safe with Emmy and friends*™ is a child protection education program designed for first grade students [23]. It consists of five 1-h sessions provided free-of-charge by trained facilitators, delivered in children’sregular classrooms once per week for five weeks. A unique program feature is the presence of an adult-size program mascot called “Emmy” who, as a child-like character, assists program facilitators by drawing attention to key themes, and modelling strategies in developmentally-appropriate ways. The *Learn to be safe with Emmy and friends*™ program addresses many of the core themes common toeffective child protection and bullying prevention programs including 1) teaching children how to recognise potentially dangerous people or situations, 2) teaching children how to respond (i.e. with rehearsed statements and positive actions) and 3) encouraging children to report or disclose past, current or future abuse or unsafe encounters to trusted authority figures [24–27]. The main topics for each of the five *Learn to be safe with Emmy and friends*™ sessions are shown in Table 1.

**Table 1 Tab1:** Overview of the *Learn to be safe with Emmy and friends*™ Program Content and Purpose

Session	Content and Purpose
1	Emotion Recognition and Early Warning Signs. Content focuses on body signals that indicate various emotions as well as emotions or feelings that might indicate danger. Strategies to assist in remaining calm and reducing anxiety or worry are also taught. This is so that children are able to recognise when they might be feeling scared or angry, and know how to calm down so that they can more effectively respond to situations.
2	Early Warning Signs and Safe/Unsafe Situations. Content focuses on early warning signs (i.e., indicators given by the body that a situation may be unsafe), discriminating safe and unsafe situations, and identifying situations that may feel unsafe but are either fun (e.g. roller coasters) or within the child’s control (e.g. a test).
3	Personal Space and Private Body Areas. Content addresses the concept of personal space and private body areas as well as teaching responses to personal space violations and information regarding disclosure.
4	Safe/Unsafe Secrets. Content focuses on examples of safe and unsafe secrets and distinguishing between these. Encouragement is also given to disclosing potentially unsafe secrets to safe adults.
5	Identification of Safe Adults and Safety Networks for Disclosure. The final session focuses on recognising and developing networks of safe adults from whom children may seek help. This includes personal networks individual to each child as well as provision of contact information for specialist services for children such as Kids Help Line.

*Learn to be safe with Emmy and friends*™ incorporates many of the delivery methods identified in effective psycho-education programsincluding active participation (i.e. role play), explicit training (specification and rehearsal of desired behaviours), standardised materials, and repeated presentations and summaries of materials as well as program materials sent home for parental review [16, 26, 28]. The program also aligns with the *Australian Curriculum: Health and Physical Education* [29].

### Control group

Waitlist-control schools will receive the school curriculum as usual and will be waitlisted for the intervention. They will participate in the pre-assessment (baseline), post-assessment (5 weeksafter baseline) and six-month follow-up data collection points for the evaluation. They will commence the program after the six-month follow-up assessment has been completed.

### Child measures

Trained research assistants will administer all child measures during individual verbal interviews at participating schools. Measures to be administered will include children’s knowledge of program concepts, intentions to use program knowledge, skills, and help-seeking strategies, actual use of program material in a simulated situation, and anxiety as a result of program participation.

#### Protective behaviours questionnaire [20]

The ProBeQ is a self-report 12-item questionnaire assessing children’s knowledge of the six core interpersonal safety concepts covered in the five *Learn to be safe with Emmy and friends*™ program lessons: (i) emotion recognition, (ii) early warning signs, (iii) private and public body parts, (iv) personal space, (v) safe and unsafe secrets and (vi) identification of safe adults as well as the program mantra ‘tell, tell, tell again until someone listens and helps’. Scores will be summed to provide a Total Protective Behaviours Knowledge score (maximum score of 22) with higher scores indicating greater knowledge of the concepts [20]. Because the ProBeQ is a test of knowledge with potential answers that range in their content and structure, psychometric properties are not calculated.

#### Application of Protective Behaviours Test-Revised (APBT-R)

The APBT-R will be administered both at pre- and post-test evaluation. This is a revised version of the original APBT developed by Dale et al. [20] as a six-item, child-report measure assessing children’s intention to apply self-protective knowledge and skills, and seek appropriate help in unsafe situations. In the APBT-R, unsafe scenarios were retained and two new safe scenarios were added. Two developmental psychologists and two child abuse prevention experts screened new safe scenarios. The APBT-R thus includes two safe and four unsafe scenarios presented to children by interviewers as verbal narratives accompanied by simple line drawings. Children’s responses for unsafe scenarios will be rated according to the degree to which they are self-protective. Scores for each scenario will be summed across unsafe scenarios to provide a Total Self-Protective Intention score with higher scores indicating greater protective behaviour intentions. Children will also be asked to rate for all scenarios whether or not each scenario is safe on a yes/no response. These responses will be marked as correct or incorrect and summed to further provide a Total Risk Accuracy score with higher scores indicating greater accuracy in classifying scenarios.

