#### Observed Protective Behaviours Test (OPBT)

This will be administered to children in the control and intervention conditions at either post-test evaluation or the six-month evaluation. A structured two-part in vivo behavioural situation has been developed by the first author expressly for this study and will be used to test children’s ability to implement the safety skills learned during *Learn to be safe with Emmy and friends*™. Part 1 will measure recognition of unsafe situations and theapplication of relevant safety skills. Children will be presented with a simulated unsafe situation enacted by an unfamiliar confederate. In the script for the unsafe situation after greeting the child, the interviewer will leave the room under the pretext of making a telephone call [30]. During the interviewer’s absence,a confederate will enter the room and ask the child to leave with them. The confederate will then remember that they have forgotten a bag and leave, asking the child to keep their presence a secret and dropping a pen to the floor as they leave. The manipulation will take approximately 1 min with the interviewer returning within 30 s of the confederate exiting and resuming the interview.

Part 2 will test children’s disclosure of the unsafe situation. In this, children will be presented with 6 prompts to disclose the presence of the confederate (e.g., “You probably didn’t notice if the pen was in the room before, did you?”). At the end of the interview, prior to administering the anxiety measure the confederate will return and the secret will be revealed. This will provide an opportunity for the interviewer to model disclosure of the unsafe situation with the child and engage in debriefing. The OPBTis based on behavioural skills training and measures used by Johnson et al. [31, 32] and Gunby et al. [33] in evaluations of children’s personal safety skills, as well as the secret-keeping scenario and seven point secret-keeping scale created by Dunkerley and Dalenberg [30].

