### Data collection

#### Assessment procedures T1-T5

Data will be collected at three sites (Brisbane, Gold Coast, and Townsville) and five main time points (T1 to T5). The Time 1 (T1) assessment (pre-test) will be conducted one week prior to program delivery. Time 2 (T2) assessment (post-test) will occur one week after program completion for the intervention group and 5 weeks after Time 1 for the waitlist control group. Time 3 (T3), Time 4 (T4) and Time 5 (T5) assessments will be conducted 6 months, 12 months and 18 months after program completion respectively.

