### Planned analyses

Mixed factorial analyses of variance (ANOVAs) will be used to examine the effectiveness of the program for primary outcomes. Analyses will be conducted to assess differences between the intervention and waitlist control conditions over time using 2 (Group: intervention, waitlist-control) x 3 (Time: T1, T2, T3) mixed ANOVAs. Primary or target outcomes include children’s knowledge of program concepts, intentions to use program knowledge, skills, and help-seeking strategies, and anxiety as a result of program participation. T-tests will be conducted to examine the difference between groups in use of program skills and disclosure during the simulated situation conducted at T2 and T3.

Following the 6-month follow-up of the children who received the program, data will be analysed to assess stability of improvement in the treatment group from post to, 6-, 12- and 18-month follow-up. One-way ANOVAs will also be conducted for these variables for the intervention group across the five time points (T1, T2, T3 and T4, T5).

Hierarchical linear modelling [37] will be used to examine any effects of the hierarchical structure of the study design. If there are hierarchical effects, this analysis will be used to account for influences of classroom (level 2) and school level effects (level 3), while examining the effects of condition (Emmy/waitlist) and within student changes over time. Regression will be used to test the mediation analyses and to examine any effects of moderators (e.g. demographic variables, parental stress, dose–response) to determine which factors may differentiate intervention effects. Intent-to-treat analyses will also be conducted to account for potential effects of differential drop-out.

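### The APBT-R is scheduled at pre-test and post-test, but the intention outcome it supplies is to be analysed out to six months between arms and 18 months within the intervention arm

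*Protocol article*

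**What the plan says.** The section on the Application of Protective Behaviours Test-Revised (APBT-R) contains the only sentence on when this instrument is given: "The APBT-R will be administered both at pre- and post-test evaluation". The same section says that ratings of the unsafe scenarios are summed "to provide a Total Self-Protective Intention score with higher scores indicating greater protective behaviour intentions". A second score, Total Risk Accuracy, comes from the same scenarios.

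The section Assessment procedures T1-T5 fixes the terms: "The Time 1 (T1) assessment (pre-test) will be conducted one week prior to program delivery", and "Time 2 (T2) assessment (post-test) will occur one week after program completion for the intervention group". T3, T4 and T5 are separate assessments at 6, 12 and 18 months.

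The Planned analyses section lists children's knowledge, intentions and anxiety as primary outcomes. It assigns them to "2 (Group: intervention, waitlist-control) x 3 (Time: T1, T2, T3) mixed ANOVAs", and then adds: "One-way ANOVAs will also be conducted for these variables for the intervention group across the five time points". It also plans to assess whether gains in the intervention group hold from post-test through the later follow-ups.

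**The concern.** The measurement section and the analysis section describe different data sets for the same primary outcome. By the article's own labels, the APBT-R sentence yields two waves. The analyses of intentions need three waves between arms and five within the intervention arm.

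Two results are at stake. The first is the six-month between-arm comparison. The Control group section has waitlist schools start the program once the six-month assessment is complete, so T3 is the last wave at which the randomised arms can be compared with one arm still untreated. If interviewers omit the APBT-R at T3, that comparison cannot be recovered later. The second is the long-term claim: the Discussion expects retention from T2 to T5, directly after a sentence that lists intentions among the outcomes expected to improve. Longer follow-up than previous studies is one of the trial's stated contributions.

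**Working it through.** No sample size or power figure bears on this point. The check sets the waves at which the APBT-R is scheduled against the waves that each analysis of intentions needs.

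**Step 1: which waves the schedule gives.** The APBT-R section names pre-test and post-test. Assessment procedures T1-T5 equates these with T1 and T2. Scheduled waves: {T1, T2}, that is 2.

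**Step 2: whether post-test could include later waves.** The article keeps them apart. The abstract separates the assessment straight after the intervention from the 6-, 12- and 18-month follow-ups. The Control group section lists a post-assessment and a six-month follow-up as different occasions. The next instrument described, the Observed Protective Behaviours Test (OPBT), is given "at either post-test evaluation or the six-month evaluation". So the term post-test does not itself cover T3.

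**Step 3: whether another instrument supplies the intention outcome.** Among the child measures, the ProBeQ scores knowledge, the OPBT scores observed behaviour and disclosure, and the RCMAS-2 scores anxiety. Only the APBT-R scores intentions.

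**Step 4: waves needed against waves scheduled**, taking the APBT-R sentence as the full schedule.

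| Use of the intention score | Waves needed | Scheduled | Without data |
|---|---|---|---|
| First hypothesis, change from pre-test to post-test | T1, T2 | T1, T2 | none |
| Mixed ANOVA, both arms | T1, T2, T3 | T1, T2 | T3 (1 of 3) |
| One-way ANOVA, intervention arm | T1 to T5 | T1, T2 | T3, T4, T5 (3 of 5) |
| Stability after post-test | T2 to T5 | T2 | T3, T4, T5 (3 of 4) |

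The degrees of freedom for time are the number of waves minus 1. In the mixed ANOVA they fall from 3 - 1 = 2 to 2 - 1 = 1. In the one-way ANOVA they fall from 5 - 1 = 4 to 2 - 1 = 1. Under stability, none of the three contrasts with T2 (at T3, T4 and T5) can be formed. The intent-to-treat analyses planned for drop-out would not help, because a wave that is not scheduled is absent for every child.

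**Step 5: scope.** The ProBeQ and RCMAS-2 sections carry no timing sentence of their own, so nothing there conflicts with the five-wave plan. The OPBT timing agrees with the t-tests planned at T2 and T3. The mismatch is confined to the APBT-R.

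**The case against.** The strongest reply is that the APBT-R sentence is loose rather than exclusive. It does not say that the two occasions are the only ones. It may simply mark a contrast with the OPBT, which has no baseline. Much of the rest of the article points to later administration: five waves of data collection, child measures given together in individual interviews, a six-month assessment in waitlist schools, and analyses that name intentions at T3 and beyond. On this view one incomplete phrase stands against a consistent plan. An instrument-by-visit table is also something that a condensed article may leave to the full protocol.

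Part of this stands. Later administration may well have been intended, so loss of the data is not established. But the reply does not settle the matter. The section on the five waves does not assign instruments to them, and inferring the schedule from the analysis plan assumes the answer. Nor is this a missing table: the article does give a schedule for this instrument, and that schedule disagrees with the analysis.

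A reader might go further and infer that the planned analyses cannot be run, or that all T3 to T5 values of both APBT-R scores will be missing. The documents do not support this. It follows only if the two named occasions are the whole schedule. It also goes too far for Total Risk Accuracy, because the Planned analyses section does not name that score or say over which waves it is analysed.

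**Conclusion.** The conflict is real and the article does not resolve it. The APBT-R is scheduled at T1 and T2, while the intention score, a primary outcome that only this instrument supplies for children, is to be analysed over T1 to T3 between arms and T1 to T5 in the intervention arm.

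The consequence is conditional. If the stated occasions are the full schedule, the intention score has no data at T3, T4 or T5, and both its six-month randomised comparison and its retention analysis are lost. If the instrument is in fact given at every wave, the defect is one incomplete sentence.

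On either reading the pre-to-post comparison of intentions in the first hypothesis stands, as do the analyses of knowledge and anxiety. Total Risk Accuracy is affected only if it is meant to follow the same waves. The point should be settled because a primary outcome is involved, an omitted T3 assessment could not be made good, and the correction is cheap.

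**What to change.** Reconcile the APBT-R section, Assessment procedures T1-T5 and Planned analyses in one of two ways.

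- **Keep the analyses.** State that the APBT-R is given at T1, T2 and T3 in both arms and at T4 and T5 in the intervention arm. If this was always intended, the cost is one sentence. If not, it adds six scenarios (two safe, four unsafe) to interviews already planned.
- **Keep the schedule.** Limit the intention analysis to T1 and T2, and withdraw the six-month comparison and the retention claim for this score. The cost is wording only, but the trial gives up longer-term evidence on a primary outcome.

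In either case, say over which waves Total Risk Accuracy will be analysed. The choice should be made before the T3 interviews begin, since after that only the second option may remain.

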#### Observed Protective Behaviours Test (OPBT)

This will be administered to children in the control and intervention conditions at either post-test evaluation or the six-month evaluation. A structured two-part in vivo behavioural situation has been developed by the first author expressly for this study and will be used to test children’s ability to implement the safety skills learned during *Learn to be safe with Emmy and friends*™. Part 1 will measure recognition of unsafe situations and theapplication of relevant safety skills. Children will be presented with a simulated unsafe situation enacted by an unfamiliar confederate. In the script for the unsafe situation after greeting the child, the interviewer will leave the room under the pretext of making a telephone call [30]. During the interviewer’s absence,a confederate will enter the room and ask the child to leave with them. The confederate will then remember that they have forgotten a bag and leave, asking the child to keep their presence a secret and dropping a pen to the floor as they leave. The manipulation will take approximately 1 min with the interviewer returning within 30 s of the confederate exiting and resuming the interview.

Part 2 will test children’s disclosure of the unsafe situation. In this, children will be presented with 6 prompts to disclose the presence of the confederate (e.g., “You probably didn’t notice if the pen was in the room before, did you?”). At the end of the interview, prior to administering the anxiety measure the confederate will return and the secret will be revealed. This will provide an opportunity for the interviewer to model disclosure of the unsafe situation with the child and engage in debriefing. The OPBTis based on behavioural skills training and measures used by Johnson et al. [31, 32] and Gunby et al. [33] in evaluations of children’s personal safety skills, as well as the secret-keeping scenario and seven point secret-keeping scale created by Dunkerley and Dalenberg [30].

#### Revised Children’s Manifest Anxiety Scale 2^nd^ Edition (RCMAS-2 Short Form), [34]

The RCMAS-2 Short Form consisting of 10 yes/no items will be used to examine whether children experience increased or decreased anxiety as a result of program participation. A Total Anxiety score can be calculated and three anxiety sub-scales include, physiological anxiety, worry, and social anxiety. (α = .82), [34]. Test-retest reliability has been calculated at .54 for the total score with a US sample [34] and .61 to .68 with an Asian sample [35].

### Parent measures

All parent measures will be administered as self-report. Measures to be administered will include family demographics, discussion monitor, program concepts checklist, satisfaction questionnaire, and a parent stress inventory.

#### Demographics

Family and child demographic information will be collected in 10 items including child gender, child age, parental gender, parental age, family structure, parental income and parental education. In these items family community engagement and the child’s social and school engagement will also be assessed.

#### Parent discussion monitor

Parents will complete a 4-item measure each week documenting:time spent reviewing the program information sheets with their children at home, time spent discussing information from *Learn to Be Safe with Emmy and Friends*™ lessons with their children and whether the content of the discussion was raised by the child or parent.

#### Parent Protective Behaviours Checklist (PPBC), [20]

The PPBC is a ten-item parent-report measure. For each item, parents’ assesses the extent to which they observed that (i) their children using self-protective skills; and/or (ii) their child understood the six concepts taught in the *Learn to be safe with Emmy and friends*™ program. Parents will indicate using a response scale of 1 (Not at all) to 4 (Always) for self-protective skills, and 1 (Unsure) to 4 (Very sure) for understanding. Scores will be summed to provide a Total PPBC score. This measure has good internal consistency (α = 0.84), [20].

#### Parent Satisfaction Questionnaire (PSQ), [20]

The 3-item PSQ will be used to assess parental subjective satisfaction with the program, perceptions of changes in their child’s presentation or behaviour since program commencement, and any additional comments via open-ended text response.

#### Parent Stress Inventory: Short Form (PSI/SF), [36]

The PSI/SF is a 36-item parent-report measure that assesses stress in parents of children aged 1 month to 12 years. A Total Stress score is calculated from three subscales including Parental Distress, Parent–child Dysfunctional Interaction, and Difficult Child. The PSI has acceptable test-retest reliability (*r* = .84) and good validity and internal consistency (α = .91), [36].

### Program performance measures

Measures of attendance and program compliance will be used in the program’s process evaluation. These will be completed by program facilitators for each of the program sessions and also by trained research assistants during audits of 10 % of all sessions at each site.

#### Attendance list

To evaluate effects due to partial versus complete attendance, program facilitators will complete an attendance record will be taken for every session.

